#### Supportive data

Anthropometric measurements, blood pressure and data on physical activity, dietary, stress and health literacy will be collected from the subject’s spouse. Socio-demographic data and family medical history will be collected from both the subject and the spouse. These variables are collected to adjust for confounding effects.

#### Sample size calculation

The sample size calculation is based on a 2-cm reduction in waist circumference, in the primary endpoint of waist circumference between the intervention and control arms at 8 months. Assuming a 5 % level of significance (alpha = 0.05), a statistical power of 90 % (beta = 0.10) and a SD of 5 cm using a two-sided *t* test, 132 women per arm are required. Taking into consideration a 20 % drop-out rate, and that 20 % will be pregnant, a total of 660 women would be randomised/enrolled to ensure 264 subjects to cover both the intervention and control arms.

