**Method/design:**

Eligible subjects will be Malaysian women in the age group 20 to 39 years, who are nulliparous, not diagnosed with diabetes and own a smartphone. With an alpha-value of 0.05, a statistical power of 90 %, 264 subjects will need to complete the study. Subjects with their spouses will be randomised to either the intervention or the control arm for an 8-month period. The primary endpoint is change in waist circumference from baseline to end of intervention period and secondary endpoints are changes in anthropometric parameters, biochemical parameters, change in health literacy level, dietary habits, physical activity and stress level. Primary endpoint and the continuous secondary endpoints will be analysed in a linear regression model, whereas secondary endpoints on an ordinal scale will be analysed by using the chi-squared test. A multivariate linear model for the primary endpoint will be undertaken to account for potential confounders. This study has been approved by the Medical Research and Ethics Committee of the Ministry of Health Malaysia (protocol number: NMRR-14-904-21963) on 21 September 2015.

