### Outcomes

#### Primary endpoint

Change in waist circumference was selected as the primary endpoint because of its validity as a superior measurement for assessing abdominal fat content and associated obesity health risk, as compared to a measure such as body mass index (BMI) [24–26]. In addition, there are existing national Malaysian data on population waist circumference, which allow for the study results to be comparable on a national level. In the present trial, the primary endpoint is predicted to provide a 2-cm reduction of waist circumference in the intervention group compared to the control group, which will reflect a reduction of central fat distribution. The reduction of 2 cm in waist circumference as a primary endpoint is based on the mean from a number of studies indicating that a decrement of waist circumference is possible with a lifestyle changing intervention over a period of 8 months [27–31]. The variation between the two time-points in these studies was small (standard deviation (SD) of 3–5) after the intervention period, and we therefore assume an expected within-person estimate of SD = 5.

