#### Randomisation

At the baseline measurement visit, subjects will be randomised into the intervention and control arms at a 1:1 allocation ratio. Random allocation sequences will be computer- generated with block sizes of six subjects. Each clinic will be provided with a sufficient number of identification (ID) numbers with randomisation codes. When a subject is enrolled in the trial, the study nurse should assign the lowest available ID number to the subject from the list of ID numbers.

The Institute for Health System Research (IHSR) under the MoH has prepared the randomisation list and these are distributed to the five designated primary health clinics in Seremban. A copy is maintained by the IHSR.

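### The enrolment target of 660 does not follow from 20% drop-out plus 20% pregnancy: those losses call for about 413 to 440 women, and 660 implies a 60% loss

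*Protocol article*

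**What the plan says.** The Sample size calculation section sets out the inputs and the result together. The target difference is 2 cm in waist circumference between arms at 8 months. The error rates are given as "Assuming a 5 % level of significance (alpha = 0.05), a statistical power of 90 % (beta = 0.10", and the evaluable number follows: "a SD of 5 cm using a two-sided *t* test, 132 women per arm are required". Two arms of 132 make 264, which the article gives as the total over both arms. The Abstract (Method/design) agrees that this is the number of completers: "264 subjects will need to complete the study".

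The section then moves from evaluable to enrolled women: "Taking into consideration a 20 % drop-out rate, and that 20 % will be pregnant, a total of 660 women would be randomised/enrolled".

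Pregnancy is a true loss to the primary analysis. The Data collection section (text following Table 2) withdraws any woman who becomes pregnant within the 8 months. The Statistical analysis section places women who become pregnant between 4.1 and 8 months in a supportive analysis. The article names no third source of loss, no safety margin and no other purpose for the enrolment figure.

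**The concern.** Two losses of 20% cannot remove more than 40% of the women. A total that shrinks from 660 to 264 loses 60%. The inputs and the result stand in the same sentence and contradict each other, so this is not a matter of detail left to a fuller document.

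The enrolment target decides how long recruitment runs and when it stops. As printed, a trial team cannot tell whether 440 randomised women would meet the plan or fall a third short of it. Nor can it tell whether a 40% loss during follow-up is what was expected or much better than expected.

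If the rates are right, the trial recruits 220 to 247 more women than its stated power needs, although the Discussion already reports low interest and expects slower recruitment. If 660 is right, the assumed attrition is 60%. In an unblinded trial where both kinds of loss occur after randomisation, an assumption of that size needs to be stated and justified.

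**Working it through.** **Inputs**

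- Difference 2 cm (Sample size calculation): "The sample size calculation is based on a 2-cm reduction in waist circumference".
- SD 5 cm (Sample size calculation; also Primary endpoint: "we therefore assume an expected within-person estimate of SD = 5"). It is taken here, as the plan takes it, as the SD of the change in each arm.
- Two-sided alpha 0.05 and power 90% (Sample size calculation).
- Equal allocation (Randomisation): "subjects will be randomised into the intervention and control arms at a 1:1 allocation ratio".
- Losses: 20% drop-out and 20% pregnancy (Sample size calculation).

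**Step 1: the evaluable number**

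n per arm = 2 × (z₀.₉₇₅ + z₀.₉₀)² × SD² / difference² = 2 × (1.960 + 1.282)² × 25 / 4 = 131.3, so 132.

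The exact t-test solution is 132.3 per arm, and 132 per arm gives 89.9% power. The plan's 132 per arm and 264 in total are reproduced.

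**Step 2: inflation for the stated losses**

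| Reading of the two losses | Share retained | Women to randomise |
|---|---|---|
| Additive (20% + 20% of all randomised) | 0.60 | 264 / 0.60 = 440 |
| Sequential (20%, then 20% of the rest) | 0.80 × 0.80 = 0.64 | 264 / 0.64 = 412.5, so 413 (414 for equal arms) |
| As printed | 264 / 660 = 0.40 | 660 |

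The common shortcut of multiplying up gives smaller figures still: 264 × 1.4 = 369.6 (370) and 264 × 1.2 × 1.2 = 380.2 (381). Neither explains 660.

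**Step 3: where 660 could come from**

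- 264 / 0.40 = 660: the share lost (40%) used as the share retained.
- 2 × 264 / 0.80 = 2 × 330 = 660: only one 20% loss applied, and a total that already covers both arms doubled again.

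Both routes give 660 exactly and both are errors. The document does not show which one occurred.

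**Step 4: what 660 delivers if the stated losses are right**

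Power is approximately Φ(2 / (5 × √(2/n)) − 1.960), with n evaluable per arm.

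- Additive: 660 × 0.60 = 396, or 198 per arm. 5 × √(2/198) = 0.5025; 2 / 0.5025 = 3.980; Φ(2.020) = 97.8%.
- Sequential: 660 × 0.64 = 422.4, or 211 per arm. 5 × √(2/211) = 0.4868; 2 / 0.4868 = 4.109; Φ(2.149) = 98.4%.
- Difference detectable with 90% power at 198 per arm: 3.242 × 0.5025 = 1.63 cm.
- Excess enrolment: 660 − 440 = 220 (50% above 440), or 660 − 413 = 247 (60% above 413).

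**Step 5: the opposite case, 440 randomised when the loss is really 60%**

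440 × 0.40 = 176, or 88 per arm. 5 × √(2/88) = 0.7538; 2 / 0.7538 = 2.653; Φ(0.693) ≈ 76% power.

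**The case against.** The best defence is that the error is conservative. The evaluable target, effect size, alpha and primary analysis are untouched. At 660 the trial has more power than it claims, and no estimate is biased. The total can be read as a floor that protects the 264 completers. The Discussion's account of busy couples and low interest also gives some reason to doubt that drop-out will stay at 20%, so cutting the target could be the riskier move.

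Most of this is fair, and it bears on which correction to choose. Step 5 shows the point: 440 enrolled under a 60% loss would leave about 76% power. But it does not rescue the sentence. The article presents 660 as the consequence of two 20% losses, not as a margin, and it ties no part of the number to the later gestational diabetes comparison. The figure is expressly a count of women, so spouses do not explain it. The full protocol might record a further reason, but no such reason would make the printed inputs yield the printed total.

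It also stands that the origin of the slip cannot be proved, and that nothing in the article suggests anyone deliberately assumed a 60% loss.

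**Conclusion.** The concern holds. The 264 evaluable women are correct; the step from 264 to 660 is not. Two 20% losses require 440 women (additive) or 413 (sequential), whereas 660 corresponds to a 60% loss. If the stated rates are true, the trial over-enrols by 220 to 247 women and has about 98% power for 2 cm. If 660 is the intended number, the stated loss rates are wrong.

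The result depends on no outside figure. It rests on the plan's own difference, SD, alpha and power, and on pregnancy counting as a loss to the primary analysis, which the article confirms. The power figures also take the SD of 5 cm at face value. Because the error is in a core design number and its own inputs contradict it, it must be corrected, even though it does not weaken the test if the stated rates hold.

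**What to change.** Reconcile the loss rates and the total in the Sample size calculation section, in one of three ways:

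- **Keep the rates and the 90% power.** State 440 randomised (220 per arm) for 264 evaluable, or 413 (414 for equal arms) if the losses are meant to be sequential, and say which reading is used.
- **Keep the rates and the 660.** State about 396 evaluable (422 if sequential) and about 98% power for 2 cm.
- **Keep the 660 and the 264.** Replace the two 20% rates with the 60% loss actually expected, and give its basis.

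The choice turns on how firm the 20% rates are, and the article gives no basis for them. If they are uncertain, the first option carries the risk shown in step 5.

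The second and third options cost one corrected sentence or a short clarifying amendment. The first changes the target of a trial that already has ethics approval, distributed randomisation lists and open recruitment, so it needs a formal amendment. It saves 220 or more enrolments, at the price of fewer women for the exploratory gestational diabetes comparison.

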#### Randomisation

At the baseline measurement visit, subjects will be randomised into the intervention and control arms at a 1:1 allocation ratio. Random allocation sequences will be computer- generated with block sizes of six subjects. Each clinic will be provided with a sufficient number of identification (ID) numbers with randomisation codes. When a subject is enrolled in the trial, the study nurse should assign the lowest available ID number to the subject from the list of ID numbers.

The Institute for Health System Research (IHSR) under the MoH has prepared the randomisation list and these are distributed to the five designated primary health clinics in Seremban. A copy is maintained by the IHSR.

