### Data collection, management and analysis

#### Study conduct

Study nurses will be trained to conduct the data collection at the five designated primary health clinics in Seremban district. At the baseline assessment, the principles of the trial will be explained again for the subject and spouse and they will be asked to provide consent by signing the consent form. One original copy of each form will be kept by the study nurse who will file the document on site. One copy of each form will be given to the subjects. The women and their spouses will have linked ID numbers by assigning each subject and spouse the same ID number with subject ID ending with the number ‘2’ and spouse ID ending with the number ‘1’ respectively.

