#### Data collection

At baseline the subjects will undergo measurements of waist circumference, hip circumference, weight, height and blood pressure by following standardised procedures based on World Health Organisation (WHO) STEPS surveillance [32]. Only the subject in the couple will provide a 10-mL blood sample to measure glycated haemoglobin A_1c_ (HbA_1c_) and a fasting lipid profile (triglycerides (TG), low-density lipoprotein cholesterol (LDL-C), high-density lipoprotein cholesterol (HDL-C) and total cholesterol (TC)). Due to the need for a fasting lipid profile analysis, the subject will be asked to come to the clinic after fasting for a minimum of 9 h. In line with this, the data collection time-points are planned to be in the morning. The European Health Literacy Tool Q-47 (HL-EU-Q47) [33] (HL-EU Consortium 2012), the Malaysian Food Frequency Questionnaire (FFQ), modified to be used in the current trial [2]; the International Physical Activity Questionnaire (IPAQ) [2]; and the Depression Anxiety Stress Scale 21-items (DASS-21) [34, 35] will be used to collect data on level of health literacy, dietary pattern, physical activity level, and stress level, respectively. Data such as socio-demographic parameters and family history of diabetes will be collected by structured interviews with the study nurse. The spouse will undergo the same data measurements, with the exception of blood sampling. At the end of the data collection, and before subject and spouse leave, data will be checked by the study nurse and site coordinator or research officer, to ensure that all data forms and questionnaires have been filled correctly. When data collection is completed the data collection forms and questionnaires will be signed-off by the study nurse and site coordinator or research officer. At the end of the baseline visit, if the subject is randomised to the intervention, the first contact with a CHP will be made. The subject and spouse will be introduced to the mobile application and it will be installed on the subject’s and spouse’s smartphone device. If the subject and spouse have sufficient time the CHP will proceed with the first contact point. If the subject and spouse do not have the time, an appointment will be set in the next 5 days either at the clinic or at the couple’s house. The same measurements, except height, socio-demographic parameters and medical history, described above will be conducted at the endpoint visit (Table 2).

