
#### Ethical, regulatory and data management considerations

The study protocol version 4.0 dated 12 August 2015 has received ethical and governance approvals by the Medical Research and Ethics Committee of the Ministry of Health Malaysia (protocol number: NMRR-14-904-21963) on 21 September 2015. The study is performed in compliance with the Declaration of Helsinki. Written informed consent will be taken from each participant prior to study enrolment by trained study nurse. The trial was registered at ClinicalTrials.gov, Identifier: NCT02617693 on 30 November 2015.

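### Coded randomisation lists sit at the enrolling clinics in fixed blocks of six, and allocation is not tied to the baseline sign-off, so concealment is weak

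*Protocol article*

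**What the plan says.** All references are to the protocol article.

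- **Where the list is.** Under Randomisation, the Institute for Health System Research "has prepared the randomisation list and these are distributed to the five designated primary health clinics in Seremban" and keeps a copy. What the sites receive is described as follows: "Each clinic will be provided with a sufficient number of identification (ID) numbers with randomisation codes".
- **Who allocates.** At enrolment, "the study nurse should assign the lowest available ID number to the subject from the list of ID numbers" (Randomisation).
- **Block size.** The sequence is computer-generated "with block sizes of six subjects". No other size is named, and the figure is published.
- **Who takes consent.** "Written informed consent will be taken from each participant prior to study enrolment by trained study nurse" (Ethical, regulatory and data management considerations). Study conduct places this at the baseline assessment.
- **Who measures.** "Study nurses will be trained to conduct the data collection at the five designated primary health clinics in Seremban district" (Study conduct). The work includes the primary-endpoint baseline: "At baseline the subjects will undergo measurements of waist circumference, hip circumference, weight, height and blood pressure" (Data collection).
- **When allocation happens.** "At the baseline measurement visit, subjects will be randomised into the intervention and control arms at a 1:1 allocation ratio" (Randomisation). Data collection then describes measurements, questionnaires, a check and a sign-off of the forms. It places the first health-promoter contact at the end of the visit. It gives no moment for randomisation.
- **Blinding.** Study design describes the trial as unblinded.

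**The concern.** Lack of blinding cannot be avoided with this intervention, but lack of concealment can. As described, the list with its codes, consent, ID assignment and data collection all lie with one clinic-based role, and no step separates them. Two biases could follow.

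1. **Selective enrolment.** A person who knows or can guess the next arm may, without intending to, press or relax the invitation, or shift a couple to another slot. The Discussion reports that busy schedules and low interest limit participation, so motivation is a plausible basis for selection. The primary model contains only treatment and baseline waist, so it would not correct for motivation.
2. **Arm-dependent baseline measurement.** Baseline waist is a manual tape reading. It enters the primary model twice, in the change score and as covariate. A reading taken with the arm known could move the treatment estimate, and the target difference is only 2 cm.

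**Working it through.** **1. The plan's own figure.** Sample size calculation gives a difference of 2 cm, SD 5 cm, two-sided alpha 0.05 and power 90%. Then n = 2 × (1.960 + 1.282)² × 5² / 2² = 131.4, rounded up to 132 per arm. This matches the plan. The point here concerns procedure and does not alter that figure.

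**2. Codes readable.** With IDs and codes on a list at the clinic, and the lowest ID always next, the next arm can be read off. Foresight is 100%.

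**3. Codes masked.** Assume that each clinic's list runs in intact blocks of six at 1:1, and that the arms already given in the current block are known, as is likely in an unblinded trial. There are C(6,3) = 20 equally likely blocks. An allocation is certain once one arm has used its three places. The best guess is always the arm with more places left.

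| Position in block | Allocation certain | Best guess right |
|---|---|---|
| 1 | 0 | 0.50 |
| 2 | 0 | 0.60 |
| 3 | 0 | 0.60 |
| 4 | 2/20 = 0.10 | 0.70 |
| 5 | 8/20 = 0.40 | 0.70 |
| 6 | 20/20 = 1.00 | 1.00 |
| **Sum** | **1.5 of 6 (25%)** | **4.1 of 6 (68.3%)** |

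Applied to the 660 women to be randomised (Sample size calculation), 0.25 × 660 = 165 allocations would be certain in advance.

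**4. Does adjusting for baseline waist help?** Let the true model be final = a + β × true baseline + τ × arm. Suppose baseline readings in the intervention arm are shifted by b, so that observed baseline = true baseline + b × arm. Substituting gives final = a + β × observed baseline + (τ − βb) × arm. Subtracting the observed baseline from both sides to form the change score leaves the arm coefficient unchanged. Adjustment therefore leaves a bias of −βb. With β close to 1 (an assumption, plausible for two readings on the same woman), nearly all of the shift passes into the estimate. Adjustment does deal with a true imbalance in baseline waist.

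**5. What a bias would cost (illustration only).** The documents give no figure for tape-reading bias, so the values below are assumptions. With SD 5 cm and 132 per arm, the standard error of the difference in change is 5 × √(2/132) = 0.615 cm. For a between-arm bias d in measured change, the two-sided error rate with no true effect is 1 − Φ(1.96 − d/0.615) + Φ(−1.96 − d/0.615).

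| Assumed bias d | Share of the 2 cm target | Actual error at nominal 5% |
|---|---|---|
| 0.25 cm | 12.5% | about 7% |
| 0.5 cm | 25% | about 13% |
| 1.0 cm | 50% | about 37% |

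**The case against.** The strongest reply is that this is a condensed article. Protocol version 4.0 and the SPIRIT file are not shown, and either may describe masking of the codes and the order of steps at the visit. The text says that clinics receive the codes. It does not say that the codes can be read before use, or that one individual nurse performs every step. Several features also narrow the risk:

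- A research officer makes the first approach, and couples agree to a baseline appointment beforehand (Screening).
- The nurse must take the lowest ID, so she cannot choose a code.
- Forms are signed off by a second person, the site coordinator or research officer, and measurement follows a standard procedure (Data collection).
- An independent organisation monitors adherence and enrolment (Data management).

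Much of this stands as a limit on size. It does not dispose of the point, which rests on what the article fixes: coded lists at the enrolling sites, one published block size, and allocation by the role that also takes consent and collects data. Being bound to the lowest ID does not help if the next arm is known, because what can then be influenced is who receives it.

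A reader might infer that nurses see every allocation in advance, or that baseline waist is measured with the arm known. The documents support neither as fact. Whether the codes are readable is not stated, and the sequence in Data collection is compatible with allocation after sign-off. A reader might also infer that the ID itself shows the arm. The only ID structure described separates woman from spouse (Study conduct). Knowledge of the arm at the endpoint measurement is a separate matter.

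**Conclusion.** The concern holds as a stated weakness in the allocation procedure and should be fixed. It is not evidence that bias has occurred. Full foresight depends on the codes being readable. With masked codes, the figures of 25% certain and 68.3% correctly guessed depend on intact blocks within each clinic and on knowledge of past arms and of the block size. Measurement of baseline waist with the arm known is possible, not stated. The error rates of 7% to 37% rest on assumed biases of 0.25 to 1.0 cm and show sensitivity only. Selection on motivation, or an arm-dependent tape reading, could not be reliably corrected by the planned model, so prevention at enrolment is the sensible course.

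**What to change.** For all remaining enrolments:

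1. Withdraw the coded lists from the clinics. Keep the readable list only at the Institute for Health System Research, which already holds a copy.
2. Reveal the arm through sequentially numbered, opaque, sealed envelopes, or by central release, only after consent has been signed and the baseline forms have passed the existing sign-off. State this order in the Randomisation and Data collection sections.
3. Issue new lists per clinic with block sizes that vary at random, and do not disclose the sizes to the sites or in publications before enrolment closes. Record the date of the change.

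If the full protocol already masks the codes and fixes allocation after sign-off, one sentence saying so settles those two parts, and only the fixed block size remains to be changed.

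The cost is new lists or envelopes, a short written procedure and a short delay at the baseline visit. Central release would also need someone reachable during the morning visits at five clinics, so envelopes are the lighter option. Women already enrolled stay as allocated.
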